#### Economic evaluation

For secondary objective 5, a cost-effectiveness analysis of advanced versus standard modality groups will be conducted. Analysis will take the form of a cost-utility analysis with cost effectiveness assessed in terms of the incremental cost per quality life year. Analysis will incorporate data on resource use and patients utility values for the period from initiation of treatment to study termination. Resource use will be assessed through review of patient charts and patient utility values will be derived using the EQ5D and MLHF. A decision model will be created to estimate long-term costs and quality adjusted life years (QALYs) for all comparators. Uncertainty within the analysis will be assessed through Monte Carlo and other simulation techniques.

#### Safety analysis

For the secondary objective 6, safety will be evaluated by documenting all adverse events. Descriptive statistics (frequency distributions, numerical descriptors) and 95% CIs will be calculated. The as-treated population will be the main analysis population for this safety evaluation.

#### Secondary analysis (PET versus CMR)

For the secondary analysis, comparing the PET and CMR modalities, potential confounding variables of the relationship between the imaging technologies and the primary endpoint will be assessed. In particular, propensity scores based on patient factors (for example, in/outpatient, NYHA class, HF duration, diabetes, atrial fibrillation) and site factors (for example, time-to-imaging, time-to-therapy) will be used in the analysis if necessary to adjust for potential differences between PET and CMR. A Cox proportional hazard models will be used to assess the occurrence of the endpoints between the imaging technologies (the model will include a group indicator variable) adjusting for any pertinent baseline differences identified. The proportional hazards assumption underlying the Cox model will be assessed. The secondary outcomes will be analyzed in a similar fashion.

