## Methods/Design

The AIMI-HF is a randomized controlled trial to compare the effectiveness of HF imaging strategies in patients with HF due to IHD. Patients enrolled will have LV systolic dysfunction due to IHD where evaluation of ischemia and viability is relevant. Patients will be allocated in a concealed fashion to standard (SPECT) versus advanced (PET or CMR) imaging. In addition, a registry will be maintained of patients undergoing standard or advanced imaging based on clinical decisions.

A survey sent to participating centers revealed that most of them could not provide stress echocardiography consistently within the requested timeframe as per the research protocol. This was especially true for dobutamine stress-echo (DSE) and viability protocols. The decision not to include this method was mainly due to statistical considerations; since if only a few centers elected to use this standard method, there may not be enough patients to adequately compare it with other methods (and site bias might also be involved).

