### Randomization

Patients will be randomized according to a pre-defined randomization scheme and availability of imaging procedures at individual participating centers. All eligible patients will be randomized to either standard or advanced imaging modalities for ischemia and/or viability testing. Participating sites with the capability for two advanced imaging modalities will then be further randomized between each modality. If randomization is not possible due to local site factors, the patient can be entered into the registry (Figure 1). The ratio of advanced to standard imaging will be 2:1.

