### Sample size

For the sample size determination, the estimated occurrence over one year of the composite clinical endpoint of cardiac death, MI, resuscitated cardiac arrest and cardiac re-hospitalization (WHF, ACS, arrhythmia) for PET is 27% and for standard care is 40%, based on the Ottawa-FIVE substudy [28] of the PARR-2 [27] study in which the composite event rates were 19% and 41%, respectively. These estimates were considered reasonable as it reflects the outcome rates that may be achievable at a facility with expertise and access to FDG PET imaging. There are no similar data upon which to draw an estimate for CMR. Considering the Schinkel *et al*. publication [38], which noted sensitivity of CMR to be between PET and standard care modalities and based on expert consensus from our IMAGE-HF workshop (16 December 2008 in Toronto, Canada), we estimate the event rate for CMR directed care would lie between the above values at 34%. Hence, an overall rate for the alternative (PET, CMR) modalities would be approximately 30%. The rates are considered conservative since the mean duration of follow-up will be 2 years, whereas the PARR-2 study was 1 year.

For the primary hypothesis, using the two-sided log-rank test for comparing advanced (PET + CMR) versus standard modalities with a 2:1 patient allocation, a sample size of 495 patients (of which 330 are allocated to the advance modality and 165 are allocated to the standard modality) would be needed in order to detect a difference after 1 year in the composite clinical endpoint of 30% for the advanced modalities (PET, CMR) compared to 40% for standard care modalities (SPECT). This is calculated with a level of significance of 0.05 and power of 80%, and assuming a uniform accrual of patients over the 2.5 year recruitment period, a 1 year minimum follow-up period and a 10% loss from each study group. The difference of 10% was considered to be a minimal clinically important difference based on a consensus of the IMAGE-HF investigators.

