For the secondary hypothesis, using the Cox regression model for comparing the advanced modalities PET versus CMR with an approximate 1:1 patient allocation, a sample size of 548 patients per modality is needed considering an anticipated rate for the composite clinical endpoint of 30% after 1 year, a level of significance of 0.05, a power of 80% and a loss to follow-up of 10%. The sample size calculation is complicated by the fact that 766 patients (383 per group) from the registry (in which patients in the registries were clinically directed to PET or CMR) will be combined in the analysis with the 330 patients (165 per group) from the randomized part of the study (in which patients in the randomized study will be randomly allocated to PET versus CMR versus standard modality) for a total of 1096 patients (548 per group). For a sample of 1096 patients, a Cox regression of the log hazard ratio of the composite clinical endpoint on the group allocation variable (PET versus CMR) with a conservative standard deviation of 0.5 (based on an approximate equal allocation to PET and CMR), achieves 80% power at a 0.05 significance level to detect a 40% increase in the hazard ratio to1.4. This increase in the hazard ratio was deemed to be the minimal clinically important difference based on a consensus among the IMAGE-HF investigators. The sample size includes an adjustment to accommodate confounding by indication for allocation patients to PET versus CMR by incorporating a multiple regression of the group allocation variable on the other covariates in the Cox regression model; a conservative estimate of this confounding was considered by taking a value of 0.25 for the multiple correlation coefficient R for the relationship between the group allocation variable and the set of covariates identified.

The total sample size is thus 1,096 + 165 = 1,261.

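### The PET versus CMR Cox comparison pools 1,096 mostly registry patients without recognising site, although modality is fixed by site wherever a centre has only one advanced modality, so the 0.05 level may not hold.

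*Protocol article*

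**What the plan says.** Under Randomization, allocation depends on which imaging each centre can offer, and the second step is limited: "Participating sites with the capability for two advanced imaging modalities will then be further randomized between each modality". Local site factors can also send a patient to the registry instead.

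Under Sample size, the PET versus CMR comparison takes "766 patients (383 per group) from the registry", who were directed clinically to one modality. They "will be combined in the analysis with the 330 patients (165 per group) from the randomized part of the study", which the plan adds up "for a total of 1096 patients (548 per group"). The same paragraph describes all 330 as randomly allocated among PET, CMR and standard imaging. By the Randomization section, that is true only at dual-modality sites.

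Under Secondary analysis (PET versus CMR), the test is: "A Cox proportional hazard models will be used to assess the occurrence of the endpoints between the imaging technologies (the model will include a group" [...]. It is adjusted for baseline differences judged pertinent. Propensity scores are to be used where needed. They draw on patient factors and on site factors, for which the examples are the times to imaging and to therapy. No site stratum, site random effect or site-clustered variance is named.

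Trial status reports 13 active sites with 20% of patients enrolled.

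**The concern.** A Cox model with a group indicator and ordinary standard errors is valid if patients are independent given the covariates. At a single-modality site every advanced-imaging patient, randomised or registry, has the same modality. That site therefore informs only a between-site contrast, and the unit of replication there is the site. What is then tested is partly whether PET centres and CMR centres have the same event hazard.

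The article itself treats centre as relevant to outcome. It says "and site bias might also be involved" when explaining why stress echocardiography was left out, and it supports the assumed PET event rate because "it reflects the outcome rates that may be achievable at a facility with expertise and access to FDG PET imaging".

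At stake is a difference in case mix, admission practice or revascularisation quality between a few centres being reported as a PET versus CMR effect, with too narrow an interval.

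**Working it through.** **1. The plan's own figure.** Inputs from Sample size: event probability P = 0.30, SD of the group variable 0.5, HR 1.4, R = 0.25, level 0.05 (two-sided reproduces the figure), power 80%, loss 10%.

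N = (1.960 + 0.842)² / [P × SD² × (ln HR)² × (1 − R²)] = 7.849 / (0.30 × 0.25 × 0.1132 × 0.9375) = 986.0. Then 986.0 / 0.90 = 1,095.6, which gives 1,096. Expected events: 0.30 × 986 = 296.

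The arithmetic is right. The formula assumes independent patients. R allows for confounding by indication, and nothing allows for clustering by site.

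**2. Size of the unstratified test with site effects.** Let τ be the SD of site effects on the log hazard, f the share of patients at single-modality sites, K the number of sites and D the number of events. The documents give neither τ nor f, so both are assumptions.

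- Under independence the variance of the log HR is v0 = 4/D.
- Site effects add τ² × Σ(a − b)², where a and b are a site's shares of all PET and all CMR patients.
- With equal-sized sites, a − b is ±2/K at single-modality sites and 0 at dual sites allocating 1:1. The sum is 4f/K.
- Actual size = 2 × [1 − Φ(1.96 × √(v0/v))], with v = v0 + 4fτ²/K.

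Example with K = 13, f = 0.5, τ = 0.2, D = 296: v0 = 0.01351, the added term is 0.04 × 4 × 0.5 / 13 = 0.00615, and v = 0.01967. The effective critical value is 1.625 and the size is 10.4%.

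| Setting | τ = 0.1 | τ = 0.2 | τ = 0.3 |
|---|---|---|---|
| 13 sites, 296 events, f = 0.25 | 5.7% | 7.7% | 11.1% |
| 13 sites, 296 events, f = 0.5 | 6.3% | 10.4% | 16.8% |
| 13 sites, 296 events, f = 0.75 | 7.0% | 13.1% | 21.8% |
| 13 sites, 296 events, f = 1 | 7.7% | 15.6% | 26.2% |
| 13 sites, about 500 events, f = 0.5 | 7.3% | 14.1% | 23.6% |
| 30 sites, 296 events, f = 0.5 | 5.6% | 7.3% | 10.3% |

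The row with 500 events matters because the article expects a mean follow-up of 2 years, so events should exceed the 296 implied by the one-year rate.

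**3. Simulation, no true PET–CMR difference.** With equal sites and 296 events, simulation agrees with the formula (f = 0.5: 5.5%, 10.6%, 17.4%). With 13 sites of unequal size, 1 to 3.5 years of follow-up and one third to all of the sites single-modality, rejection was 6–14% at τ = 0.1, 12–31% at τ = 0.2 and 20–46% at τ = 0.3. With 30 unequal sites and τ = 0.2 it was 7–18%. With every site dual and allocating 1:1, it stayed at about 5–6%.

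**4. Effect of the planned adjustment.** If measured site factors removed half the between-site variance (13 sites, f = 0.5), simulated size would be 8.3% at τ = 0.2 and 11.5% at τ = 0.3.

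**5. Candidate remedies.** A site-stratified test rejected about 3–7% of the time wherever some sites were dual. A Wald test with uncorrected site-clustered variance and a t reference on K − 2 degrees of freedom still rejected about 6–11% at 13 sites. Score forms of the clustered test gave 4–6% in one implementation and 1–2% in another, so the exact form matters.

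The stratified test uses only events at dual sites, so power = Φ(√[296 × (1 − f) × 0.25 × 0.9375] × ln 1.4 − 1.96). This gives 80% at f = 0, 68% at f = 0.25, 51% at f = 0.5 and 29% at f = 0.75. At f = 1 there is no within-site contrast. Longer follow-up helps: at τ = 0.2 and 1 to 3.5 years, simulated power was about 88% with two thirds of sites dual and 55% with one third.

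**The case against.** The strongest reply is that the article names no variance estimator. Stratification by centre and robust errors are often left to an analysis plan, which is not shown here. That is fair as far as silence goes. But the article does fix a pooled Cox comparison, a sample size from an independent-patient formula and a specific way of handling site, and these can be judged as stated. An unseen plan may already cure the problem.

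A second reply is that site is not ignored, because the propensity score lists site factors and the list is open. This stands in part. The score is conditional, its examples are process times rather than site itself, and covariate adjustment leaves residual site variance outside the standard error.

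A third is that the two supporting remarks come from other contexts: one explains the exclusion of stress echocardiography, the other justifies an event rate. Neither supplies a between-site variance. That is correct; they show only that the authors regard centre as relevant.

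A reader might also infer that modality follows site for many patients, or that the test demonstrably rejects well above 5%. The documents do not support either. No share of single-modality sites is given, the 13 sites are an interim count with further sites expected, and with τ = 0.1 or with 30 sites the excess can be small.

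**Conclusion.** The concern holds conditionally. The stated PET versus CMR analysis does not recognise site, while the randomisation rule makes modality a site attribute wherever only one advanced modality is available. If a material share of patients is at such sites, the 0.05 level is not held.

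At 13 sites the assumed range is about 6–12% at SD 0.1 (one simulated setting reached 14%). At SD 0.2 it is about 10–30%, falling to 7.7% if only a quarter of patients are at single-modality sites and events number 296. It is higher again at SD 0.3. At 30 sites and SD 0.2 it is about 7–18%. There is no inflation if all sites are dual and allocate 1:1.

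It would be wrong to conclude that the sample size is miscalculated: 1,096 reproduces exactly. It would also overstate the stakes to say that this comparison drives 1,096 of the 1,261 patients. The primary comparison already needs 330 advanced-imaging patients, so PET versus CMR adds 1,096 − 330 = 766. It is a secondary hypothesis, and the primary comparison was not tested here.

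**What to change.** In Secondary analysis (PET versus CMR):

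- Pre-specify a site-stratified Cox analysis, which uses within-site contrasts at dual-modality sites, with randomised or registry source as a further stratum. Report it alongside the pooled estimate. Keep the patient-level adjustment, since site strata do not remove confounding by indication among registry patients.
- For the pooled 1,096-patient estimate, use a site-clustered variance with a named small-sample correction and a t reference on (sites − 2) degrees of freedom. State that this corrects the interval but leaves confounding by site in the hazard ratio.
- Describe the pooled result as non-randomised and partly between-site, and align the Sample size description of the 330 with the Randomization section.
- Report the number of single-modality sites and the share of patients at them.

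This changes wording only and needs no new data or patients. The cost is wider intervals and, for the stratified analysis, less than the stated 80% power for HR 1.4 when few sites are dual: on the protocol's own inputs 68%, 51% and 29% with 25%, 50% and 75% of patients at single-modality sites.

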#### Missing data

‘Missingness’ is considered to be missing at random (MAR) and mixed methods repeated measures (MMRM) and multiple imputation techniques will be used for handling missing data. In particular, for continuous outcomes at multiple time points MMRM will be used.

### Study management

The IMAGE-HF trial is managed by an Executive Committee consisting of clinicians specialized in diagnostic imaging and/or heart failure and experts in biostatistics, physics and radiochemistry, as well as a larger Steering Committee consisting of members of the Executive Committee and representatives of all the initial study centers. (Table 3) In addition there is an events adjudication committee, which will independently review and adjudicate each clinical event blinded to treatment randomization. Since all the imaging approaches are part of standard clinical practice, no interim analysis is planned, but there will be independent data safety monitoring board (DSMB), which will review the safety data on a periodic basis; the frequency of the meetings and the charter governing the DSMB will be finalized at the first meeting of the DSMB.

**Table 3 T3:** Imaging Modalities to Assist with Guiding Therapy and the Evaluation of Patients with Heart Failure (IMAGE-HP) participating

## Trial status

At the time of this manuscript preparation, the IMAGE IA trial is currently in the second year of active enrollment. We have enrolled a total of 249 patients, representing 20% of anticipated total enrollment. The study is active in a total of 13 sites across Canada and Finland. We anticipate study completion of enrollment by December 2015.

## Abbreviations

AIMI-HF: Alternative Imaging Modalities in Ischemic Heart Failure; CABG: Coronary artery bypass graphing; CAD: Coronary artery disease; CKD: Chronic kidney disease; CMR: Cardiac magnetic resonance imaging; DSE: Dobutamine stress echocardiography; DSMB: Data safety monitoring board; EF: Ejection fraction; eGFR: Estimated glomerular filtration rate; FDG PET: Fluorodeoxyglucose (^18^F) positron emission tomgoraphy scan; HF: Heart failure; IHD: Ischemic heart disease; IMAGE-HF: Imaging Modalities to Assist with Guiding Therapy and the Evaluation of Patients with Heart Failure; ITT: Intent-to-treat; JVP: Jugular venous pressure; LVEF: Left ventricular ejection fraction; MAR: Missing at random; MDRD: Modification of Diet in Renal Disease; MI: Myocardial infarction; MLWHF: Minnesota Living with Heart Failure; MMRM: Mixed methods repeated measures; NYHA: New York Heart Assocation Functional Class; PARR-2: PET and Recovery Following Revascularization; PCI: Percutaneous coronary interventsion; PET: Positron emission tomography; QA: Quality assurance; QALYS: Quality adjusted life years; SOPs: Standard operating procedures; SPECT: Single photon emission computed tomography; STEM: Segment elevation myocardial infarction; STICH: Surgical treatment for ischemic heart failure.
